**Figure 3. A157244FIG3:**
[figure not shown]
CONSORT diagram illustrates the flow of participants through each stage of a randomized trial

### 4.1. Assignment of Interventions: Allocation Sequence Generation

This randomization was conducted using a simple randomization technique to allocate participants in a 1:1 ratio to one of two sequence groups: Sequence 1, where participants received meal A in the first week and meal B in the second week; and sequence 2, where participants received meal B in the first week and meal A in the second week. Fifteen participants were allocated to each sequence group. 

The random number table was used to generate the allocation sequence. To ensure allocation concealment, an independent individual not affiliated with the study placed the random sequence into opaque, sealed envelopes. At baseline, each participant randomly selected one envelope, and the sequence inside determined the order in which they received the meals. Additionally, participants were blinded to the order of meal administration. Meals were prepared in advance to appear as identical as possible, with minimal distinguishing features, so that participants did not know which diet they were receiving at any stage. Standardization emphasized uniform meal presentation with minimal features to maintain participant blinding to the meal order. 

This study was a randomized controlled trial employing a crossover design and involving a total of 30 participants (15 women and 15 men). During the first phase, each participant received one of the two meal interventions: Either an HP-HF-LC meal or an HP-LF-HC meal. In the second phase, participants received the alternate meal. Due to the crossover design and the differences in food components between phases, blinding was feasible only for the sequence groups. 

### 4.2. Concealment Mechanism

Since participants consumed both intervention meals, the concealment applied only to the order in which the meals were administered.

### 4.3. Implementation

The registration of participants, generation of the allocation sequence, and assignment of the intervention type were managed by an individual who was independent of the research team. 

### 4.4. Data Collection and Management

#### 4.4.1. Blinding

Blinding is feasible only for the sequence groups.

#### 4.4.2. Procedure for Unblinding if Needed

Blinding is not applicable in this study.

### 4.5. Assessment and Outcomes

#### 4.5.1. Indirect Calorimetry Procedure

Participants began by resting in a supine position for 15 minutes to allow their heart rate to stabilize. After this period, a calorimetry mask was placed on their faces, and they breathed normally for 20 minutes. During this time, the indirect calorimetry device measured oxygen consumption and carbon dioxide production, enabling the calculation of resting energy expenditure, food oxidation rates, and respiratory rate. It was essential that participants remained awake, alert, and still throughout the calorimetry period. 

The indirect calorimetry measurements were conducted in five stages: Once before the intervention in a fasting state, and then at 1-, 2-, 3-, and 4-hours post-intervention. Due to the high sensitivity of indirect calorimetry, strict conditions were maintained to ensure maximum measurement accuracy. 

Calorimetry was performed in a separate, quiet room, isolated from other participants and distinct from the sampling area. Movements within the room were minimized, and the temperature was controlled between 22 and 24 degrees Celsius. Participants were required to fast for 10 - 12 hours before the start of the calorimetry measurement, with their evening meal being consistent with their usual diet. They were also advised to avoid strenuous physical activity on the day of the visit, arrive at the study center by vehicle, and refrain from smoking. 

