## 2. Objectives

The primary objective of this study is to evaluate the effects of two distinct meal compositions—high-protein, high-fat, low-carbohydrate (HP-HF-LC) and high-protein, low-fat, high-carbohydrate (HP-LF-HC) meals—on appetite response (AR), RMR, diet-induced thermogenesis (DIT), and respiratory quotient (RQ) in adults aged 18 to 65.

The secondary objective is to assess the postprandial effects of HP-HF and HP-LF meals on blood glucose, low-density lipoprotein cholesterol (LDL-C), high-density lipoprotein cholesterol (HDL-C), triglycerides (TG), serum insulin, thyroid-stimulating hormone (TSH), thyroxine (T4), and epinephrine.

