## 3. Methods

### 3.1. Trial Design

This study was structured as an acute, randomized crossover clinical trial to evaluate two meals with identical protein content but differing in fat and carbohydrate proportions (HP-HF-LC and HP-LF-HC). Each participant consumed both meals on separate days, with a minimum one-week washout period between sessions to eliminate carryover effects. The stages of intervention and evaluation were outlined in Figure 1. 

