**Figure 1. A157244FIG1:**
[figure not shown]
Stages of intervention and evaluation

Two days prior to the intervention, participants were contacted and instructed to abstain from alcohol consumption, strenuous physical activity, and any dietary changes until their scheduled visit. On the day of the intervention, participants were required to arrive at the Imam Reza Hospital Research Center at 7:00 a.m., using personal vehicles or public transportation while minimizing physical exertion. Participants observed a 12-hour fasting period prior to their arrival, during which they could consume only water and had to refrain from smoking. 

Upon arrival, eligibility for participation was reconfirmed, followed by the measurement of anthropometric parameters. Participants completed an appetite questionnaire and underwent an indirect calorimetry (IC) assessment in a fasting state. Immediately after the IC assessment, a venous blood sample was collected. Participants then consumed the assigned intervention meal within 10 minutes under researcher supervision. 

During the postprandial phase, IC and appetite response assessments were conducted four times at one-hour intervals. Blood samples were collected twice: One hour after the meal and again during the final hour of the assessment. All tests were performed under standardized conditions and administered by the same personnel to ensure consistency. Figure 2 provided a schedule of the intervention and assessments, with time intervals selected based on prior studies. 

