### 3.3. Sample Size

Due to the novelty of our study and the absence of prior similar research, the sample size was determined based on the study by Soares et al. (12). The respiratory exchange ratio was selected as the main variable, with the alpha error set at 0.05 and the beta error at 0.2. The sample size was calculated using the two-mean test formula for a quantitative trait in two independent groups. To account for potential attrition, the final sample size was determined to be 30 participants.

$$n=\frac{{\left(Z_{1-\frac{\alpha }{2}}+Z_{1-\beta }\right)}^{2}\left(\sigma_{1}^{2}+\sigma_{2}^{2}\right)}{{\left(\mu_{1}-\mu_{2}\right)}^{2}}$$

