### 4.6. Monitoring and Adherence

To monitor and ensure adherence to the intervention protocol, five nutrition experts, well-versed in the study procedures, were involved at all stages. These experts oversaw anthropometric measurements, blood sampling, calorimetry, meal distribution, and participants’ resting periods. 

Participants were contacted three days prior to their scheduled visit to confirm the date and time. Additionally, they received a follow-up call the night before to review fasting requirements and attendance instructions. 

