## 5. Discussion

Previous attempts to combat obesity have not yielded the expected results, contributing to the current epidemic, which has emerged as a global concern. The challenges associated with obesity are complex, extending beyond immediate health issues to impose a substantial burden on society and future generations (13). Generally, obesity and overweight conditions result from an imbalance between energy intake and expenditure. A common challenge in weight loss efforts is metabolic adaptation, a process in which the body’s basal metabolic rate decreases in response to reduced food intake and caloric consumption. Exploring strategies that reduce energy intake while preserving or enhancing energy expenditure may be critical for achieving effective weight reduction and ensuring long-term maintenance (6, 14). 

Research highlights the significant role of proteins in increasing energy expenditure and promoting satiety compared to carbohydrates and fats. It suggests that increasing the proportion of protein within total caloric intake can enhance feelings of fullness, even when meal sizes are reduced (15-17). However, there is ongoing debate about whether carbohydrates or fats have a greater effect on increasing metabolic rate, particularly RMR. 

The goal of this study is to identify a protein-rich dietary composition with varying fat and carbohydrate content that optimizes RMR while minimizing any negative impacts on basal metabolism. This approach could provide an effective strategy for managing overweight and obesity without adverse side effects.

Since this is a protocol study, the actual limitations will become more evident during the implementation phase. Nonetheless, some anticipated limitations include selection bias, as individuals volunteering for this study may differ in motivation or adherence compared to the general population. Reporting bias is another potential issue, as participants self-report their food intake, which may result in less accurate data. Additionally, generalization is limited to overweight and obese populations, as the study is specifically designed to address metabolic responses within these groups. Further studies will be needed to determine whether the outcomes are consistent in other populations. These challenges will be addressed following the study to ensure the results are presented with a robust perspective.

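### The evening meal before each visit need only be habitual, so a participant's two pre-visit dinners can differ and may add within-person noise; the fasting window is also worded inconsistently (minor)

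*Protocol article*

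**What the plan says.** The pre-visit rules are spread over several sections of the protocol article.

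- **Evening meal.** Section 4.5.1 describes the overnight fast "with their evening meal being consistent with their usual diet".
- **Two days before.** Under section 3.1, participants were "instructed to abstain from alcohol consumption, strenuous physical activity, and any dietary changes until their scheduled visit".
- **Spacing of visits.** Section 3.1: "Each participant consumed both meals on separate days, with a minimum one-week washout period between sessions to eliminate carryover effects".
- **Contacts.** Section 4.6: "Participants were contacted three days prior to their scheduled visit to confirm the date and time", and in addition "they received a follow-up call the night before to review fasting requirements and attendance instructions".
- **Fasting time.** Section 3.1 gives 12 hours counted to a 7:00 a.m. arrival. Section 4.5.1 gives 10 to 12 hours counted to the start of calorimetry, which comes after a 15-minute supine rest. Section 4.5.2 says attendance was scheduled so that the fast stayed within 12 hours.

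The outcomes concerned are the main ones. The primary objective in section 2 is the effect of the meals "on appetite response (AR), RMR, diet-induced thermogenesis (DIT), and respiratory quotient (RQ) in adults aged 18 to 65". In section 3.3, "The respiratory exchange ratio was selected as the main variable" for the sample size.

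**The concern.** A crossover gains its precision from each participant serving as their own control, so conditions that can be held constant within a person are worth holding constant. The dinner before the fast is one of these. Section 4.5.1 itself says that calorimetry is highly sensitive and needs strict conditions, and it fixes room temperature, posture, rest and transport. For dinner it asks only that the meal be habitual.

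A habitual diet is not one meal. A participant could eat a fatty dinner before one visit and a starchy one before the other and comply both times. RQ reflects which fuel is being oxidised, and fat against carbohydrate is the contrast that the test meals create. Any effect of dinner that outlasts the fast would enter the fasting and postprandial values as visit-to-visit variation. What is at stake is precision.

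The fasting wording is a lesser matter: read literally, the sections cannot all be met at once.

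**Working it through.** **1. Do the stated rules match the two dinners?**

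| Rule | Section | Constrains | Links visit 2 to visit 1? |
|---|---|---|---|
| Habitual evening meal | 4.5.1 | kind of diet | no |
| No dietary changes from two days before | 3.1 | departure from habit | no |
| Call three days before | 4.6 | date and time | no |
| Call the night before | 4.6 | fasting and attendance | no |
| Fasting limits | 3.1, 4.5.1, 4.5.2 | time of last intake | indirectly, timing only |

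No row fixes what or how much is eaten across the two visits. On timing, 12 hours before 7:00 points to about 19:00 at both visits; section 4.5.1 alone leaves a two-hour range. Composition and size are therefore the main freedom, and timing a smaller one.

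**2. How much precision could this cost?**

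The article gives no variance components, so there is no figure of its own to reproduce and the loss cannot be computed. The following is an illustration under assumptions.

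- f = share of the variance of the within-person meal contrast due to unmatched dinners (assumed).
- Power with matched dinners = 80%, from the planning values alpha 0.05 and beta 0.2 in section 3.3 (assumed to hold for the crossover comparison).
- n = 30, section 3.3.

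Formulas: the standard error with unmatched dinners, relative to matched, is 1/√(1−f). The effective n is 30(1−f). Power is Φ(2.8016·√(1−f) − 1.96), where 2.8016 is the sum of the normal quantiles for two-sided 5% and 80% power.

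| f | SE factor | Effective n | Power |
|---|---|---|---|
| 2% | 1.010 | 29.4 | 79.2% |
| 5% | 1.026 | 28.5 | 78.0% |
| 10% | 1.054 | 27.0 | 75.7% |
| 20% | 1.118 | 24.0 | 70.7% |

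For f = 10%: √0.90 = 0.9487; 2.8016 × 0.9487 − 1.96 = 0.698; Φ(0.698) = 75.7%.

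Nothing in the article says which row applies. Analysing change from each visit's fasting value would remove part of the effect.

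**3. Does it bias the comparison of meals?**

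Meal order is randomised (section 4.1), so dinners do not line up systematically with one test meal. Each visit also has calorimetry, appetite and blood measured fasting before the meal (section 3.1). No bias is expected.

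**4. Clock check of the fast.**

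- Section 3.1: 7:00 minus 12 h = 19:00 as the latest intake.
- Section 4.5.1: 15 min of rest before the mask, so calorimetry starts at 7:15 at the earliest.
- 19:00 to 7:15 = 12.25 h as a minimum, before any time for anthropometry and the appetite questionnaire.

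This is at least 15 min over the 12-hour maximum in sections 4.5.1 and 4.5.2. No upper limit for the overrun follows, because 19:00 is the latest intake and an earlier dinner also satisfies section 3.1.

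**The case against.** The strongest reply is that a journal article condenses a fuller protocol, and that an instruction to repeat a particular dinner is the kind of detail left to it. Asking for a habitual meal is also a legitimate choice. This has weight, but the article does state the evening-meal rule, and that rule as written admits different dinners. The point is about the rule given, and it does not show that no further instruction existed.

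A second reply is that no consequence is demonstrated. That stands as to size. The shares f are assumed, and so is the 80% starting point. Section 3.3 uses a formula for independent groups and then allows for attrition, while section 4.10 replaces participants who cannot complete. If the unstated planning means and standard deviations are right and the within-person correlation is not negative, a paired comparison in 30 completers would have at least 80% power. The table may therefore overstate the threat.

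Third, the fasting limits already hold dinner time fairly steady, and section 4.5.2 presents its limit as a consistency measure. This stands for timing but does not touch composition or size. The conflict in wording is small, disappears if 12 hours is read as a nominal overnight fast, and would be largely shared by both visits.

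Fourth, the article is mostly in the past tense, so some or all visits may be over. That limits the remedy. Section 5 does list inaccuracy because "participants self-report their food intake" as a limitation, but that concerns reporting and not unmatched dinners.

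A reader might infer that uncontrolled dinners bias one meal against the other, or that the trial is materially underpowered because of them. The documents support neither: order is randomised with a fasting baseline at each visit, and there are no data on how much dinner effect survives the fast.

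**Conclusion.** The point holds as a modest one about precision, worth considering rather than requiring. The stated rules let a participant's two pre-visit dinners differ, which may add within-person noise to RQ, RMR, DIT and appetite. The amount is unknown and possibly small; the power figures of 79.2% down to 70.7% depend wholly on assumed variance shares of 2% to 20% and an assumed 80% start. The fasting-window conflict is real on a literal reading, at least 12.25 h against a 12 h maximum, but it is mainly editorial.

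**What to change.** **Visits still to come.** For each participant whose visit 2 is pending, record the self-chosen usual dinner eaten before visit 1 and ask for the same dinner at the same clock time before visit 2. If visit 1 has already taken place and its dinner was not recorded, treat it as a completed visit. Give the reminder in the contact already made two to three days before (sections 3.1 and 4.6), since the night-before call may come after dinner. The habitual-diet intent is kept.

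**Completed visits.** Name unmatched dinners as a limitation in section 5 and, if recorded, report the actual fasting duration by visit.

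**Wording.** State one fasting window, anchored to the start of calorimetry and the same at both visits, and use it in sections 3.1, 4.5.1 and 4.5.2. Which window applies is for the sponsor to decide.

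**Cost.** About one sentence for the dinner rule, one extra item in an existing contact and the wording edits. The downside is a small burden on participants, who must note one dinner and repeat it.

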#### 4.5.2. Appetite Evaluation

On the day of the study, participants completed a paper questionnaire at three key points: Before the intervention, one hour after the intervention, and at the conclusion of the intervention. This questionnaire assessed levels of satiety and hunger, with responses evaluated using a visual analog scale. To ensure consistency, participants’ attendance times were scheduled so that fasting did not exceed 12 hours. All measurements and evaluations were conducted between 7:00 am and 12:00 pm.

#### 4.5.3. Blood Sampling Protocol

Blood samples were collected in three phases: At baseline (fasting state), one hour after the intervention, and four hours after the intervention. The primary objective was to compare blood parameters at one hour and four hours post-intervention with those measured at the fasting baseline. The parameters to be analyzed included blood glucose, LDL, HDL, cholesterol, TG, TSH, T4, and epinephrine.

#### 4.5.4. Anthropometric Measurements

Anthropometric measurements were conducted at the beginning of each participant's visit. An experienced nutritionist at the research center was responsible for these evaluations to minimize measurement errors. To ensure accuracy, participants had to be confirmed as fasting and were instructed to avoid consuming liquids, including water, prior to the measurements. Whenever possible, participants were assessed with an empty bladder. Height was measured using a stadiometer with 1 mm accuracy, with participants standing barefoot. Weight was measured using a clinical scale with an accuracy of 100 g, with participants dressed in minimal clothing. Waist circumference was measured at the midpoint between the lower edge of the ribs and the top of the iliac crest, ensuring that the measuring tape was parallel to the ground. Abdominal circumference was measured horizontally at the level of the navel, and hip circumference was measured at the widest part of the buttocks. Body composition was analyzed using a bioelectrical impedance analyzer.

### 4.6. Monitoring and Adherence

To monitor and ensure adherence to the intervention protocol, five nutrition experts, well-versed in the study procedures, were involved at all stages. These experts oversaw anthropometric measurements, blood sampling, calorimetry, meal distribution, and participants’ resting periods. 

Participants were contacted three days prior to their scheduled visit to confirm the date and time. Additionally, they received a follow-up call the night before to review fasting requirements and attendance instructions. 

### 4.7. Data Management and Analysis

Data from anthropometric measurements, blood sampling, and calorimetry were recorded by the lead researchers using Microsoft Excel. Each participant's data was coded to ensure confidentiality, with only the principal researchers having access to identifying information. The coding system consisted of a three-digit number followed by letters A to E. The first digit (1 or 2) indicated the type of intervention, the next two digits denoted the participant number, and the letters represented the fasting stage and subsequent hours post-intervention. 

Data were reported as means ± standard deviations for continuous variables that followed a normal distribution, while non-normally distributed continuous variables were presented as medians along with interquartile ranges. Categorical variables were summarized using frequency distributions expressed as percentages. To compare conditions, independent two-sample *t*-tests were employed. Statistical analyses were conducted using generalized linear models (GLM) within SPSS version 22. The carryover effect was assessed, and if found significant, the influence of time and type of meal was analyzed. In the absence of a significant carryover effect, comparisons were made in parallel during the first period using covariance analysis. A two-factor repeated measures design was evaluated using generalized linear mixed models to examine the impact of time and type of meal across various phases of the study.

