### 4.11. Expected Outcomes

#### 4.11.1. Primary Outcomes

The primary expected outcomes included the results of five indirect calorimetry measurements for each participant at each stage, as well as assessments of satiety conducted before the intervention, one hour after, and four hours after the intervention.

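### The data code carries the meal as a fixed first digit, so it cannot mask those who handle calorimetry, blood or analysis data, and the statements on blinding conflict

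*Protocol article*

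**What the plan says.** **The code.** Section 4.7 gives each participant's data a three-digit number and a letter: "The first digit (1 or 2) indicated the type of intervention, the next two digits denoted the participant number". The letters A to E mark the fasting stage and the hours after the meal. The stated purpose is confidentiality: "data was coded to ensure confidentiality, with only the principal researchers having access to identifying information". The same paragraph says who enters which data: "Data from anthropometric measurements, blood sampling, and calorimetry were recorded by the lead researchers using Microsoft Excel".

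**Blinding.** Section 4.1 has the meals prepared to look alike "so that participants did not know which diet they were receiving at any stage". The same section closes by limiting blinding to the sequence groups, and gives as a reason that the food components differ between phases. Section 4.4.1 repeats the limit: "Blinding is feasible only for the sequence groups". Section 4.4.2 reads: "Blinding is not applicable in this study".

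**People.** Under section 4.3, someone outside the research team manages registration, the sequence and assignment. Under section 4.6, five nutrition experts oversee calorimetry, blood sampling and the handing out of meals. Under section 4.8, one operator assays all samples in a batch after the last participant has finished.

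**The concern.** The allocation steps separate the meal from the people running the trial, through an independent person, sealed envelopes and look-alike meals. The coding rule then puts the meal into the identifier of every coded record. Laboratory work, data cleaning and analysis are the steps where masking is easiest, because they do not depend on the meals looking alike, and this rule gives that masking away.

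What is at stake is the handling of the data by people who can see the meal. Section 4.7 leaves several choices that depend on the data: how to summarise each variable according to its distribution, a branch that turns on the carryover assessment, and a mix of t-tests, generalized linear models, analysis of covariance and mixed models. A choice influenced by the meal label acts in the same direction in every participant, so the crossover does not cancel it. Calorimetry is one of the primary outcomes (section 4.11.1), so the exposure is not confined to secondary endpoints.

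Separately, a reader of sections 4.1, 4.4.1 and 4.4.2 cannot tell who was masked to what.

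**Working it through.** This is a check of the text and a count. The article gives no figure for this point that could be reproduced.

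**1. How many codes carry the meal.** Inputs: 30 participants (section 3.3), two meals each (section 3.1), five stages A to E (section 4.7). 30 × 2 × 5 = 300 codes at most. Calorimetry uses all five stages (section 4.5.1); blood uses three of them (section 4.5.3).

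**2. What one known pairing reveals.**
- Present rule: the digit means the same meal for everyone. One pairing of digit and meal decodes 300 of 300 codes.
- First digit as visit number: section 4.1 puts 15 participants in each sequence, so at visit 1 the digit stands for meal A in 15 and meal B in 15. The digit alone says nothing about the meal. Learning one participant's pairing decodes that participant's two sessions, 2 × 5 = 10 codes, or 10/300 = 3.3%.

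**3. Who could learn the key.** The digit does not name the meal, so a key is needed. No section says that the key was withheld from anyone. The five experts of section 4.6 oversee meal distribution as well as measurement, so a meal and a code could be seen together. The lead researchers record the data. The laboratory operator and the analyst are not said to be masked.

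**4. The blinding statements side by side.**

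| Section | Statement in substance |
|---|---|
| 4.1, middle | Participants never know which meal they are eating |
| 4.1, end, and 4.4.1 | Only the sequence can be blinded; 4.1 adds that the food differs between phases |
| 4.4.2 | Blinding does not apply |

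The first two could be brought together if being unaware of the order is taken to mean being unaware of the meal at each session. The reason added at the end of section 4.1 works against that reading. The third contradicts both as worded.

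**5. Does this reach the appetite outcome?** Satiety is primary: section 4.11.1 lists it "as well as assessments of satiety conducted before the intervention, one hour after, and four hours after the intervention". Section 4.5.2 says "participants completed a paper questionnaire at three key points", answered on a visual analog scale, so the rater is the participant. Section 4.7 names anthropometric, blood and calorimetry data beside the code and does not name the appetite form. Nothing says that the code was written on that form or that participants saw it. The route from the code to the appetite scores is not documented.

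**6. Period.** The code holds meal, participant and stage, but not first or second visit. Section 4.7 plans a carryover assessment and a first-period comparison, and both need period. Period can be recovered by joining the participant number to the allocated sequence, so it is not lost, but it is not on the record.

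**The case against.** The strongest reply is that the code breaks no promise. The article offers masking of participants and of meal order only; it never undertakes to mask assessors, laboratory or analyst, and the code is introduced for confidentiality. Most other outcomes come from a device or an assay kit. On-site staff probably knew the meal whatever the label, because the same team oversaw its distribution. Section 4.4.2 may simply mean that no unblinding procedure is needed. The article is written largely in the past tense and registration was retrospective (section 3.2.1), so relabelling at the bedside may come too late.

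Much of this stands. A reader might infer three stronger things that the documents do not support:
- *That the code was on appetite forms and blood tubes, so that anyone holding one could tell the meal.* No section says where the code was written, and the digit needs a key.
- *That the code unmasked a subjective primary outcome.* Satiety is rated by the participant, and participants are not said to have seen or understood the code.
- *That a bias of a given size entered the readings.* The article describes no hand scoring, no discretion to repeat a calorimetry run and no outlier rule. The count of 300 is the number of codes affected and does not measure bias.

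The reply does not dispose of the rest. The rule as written rules out masked assay, cleaning and analysis for anyone with the key, although these were within easy reach. If section 4.4.2 was meant to concern unblinding only, its wording should say so.

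**Conclusion.** The point holds in limited form. The code in section 4.7 identifies the meal on every coded record to anyone who knows or infers one pairing, and so it offers no masking to those who handle calorimetry, blood or analysis data. That sits poorly with the masking aim of section 4.1. The statements in sections 4.1, 4.4.1 and 4.4.2 contradict each other as worded and must be reconciled whatever is decided about the code.

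Its extent is up to 300 codes; its effect on the results cannot be estimated from the article. This is a moderate weakness of conduct and reporting, worth correcting because correction costs almost nothing. It is not evidence that the appetite outcome was unmasked or that any result is biased. The conclusion assumes that the digit was used as described and that the key was not withheld, on which the article is silent.

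**What to change.** 1. Make the first digit the visit number (1 = first session, 2 = second session). Period then stands on each record for the planned carryover and first-period analyses.
2. Have the independent person who already manages the sequence hold the key linking participant and visit to meal, and release it only when assays are done and the data are cleaned and locked.
3. If data are already collected, have the file recoded in this way before analysis, and withhold the key in the same manner.
4. Reconcile sections 4.1, 4.4.1 and 4.4.2 into one statement: participants (through look-alike meals), the laboratory operator and the analyst are masked to meal; on-site staff involved in meal distribution are not. Claim masking of the operator and analyst only for steps still to be done under the withheld key.

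The cost is a relabelling step, a key kept by the independent person and a few sentences of text. No new role is needed. The change will not mask on-site staff who see the meals, and the text should not claim that it does.
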